**09 Disease monitoring and treatment of progressive disease**

**9.1** *Disease monitoring*  In case of a PSA rising and/or suspected clinical local (new or progressive palpable prostate nodule) or distant failure (bone pain, low extremity edema, unjustified dyspnea, etc.):

- Bone scan

- CT of the thorax, abdomen and pelvis

- Bone CT or MR to confirm the bone scan data

- TRUS or MR of the prostate

- Prostate biopsy

- Choline PET scan (optional).

**9.2** *Treatment of progressive disease*

The timing and nature of treatment in case of progressive disease will be left at the decision of the individual physician.

**10 Statistical considerations, sample size, data analysis and reporting**

The main objective of the trial is to investigate the late toxicity and freedom from biochemical failure.

This is a single-institution, prospective, phase III randomized trial designed to randomize patients with high risk prostate cancer to receive 80 Gy in 40 fractions in 8 weeks at 2.0 Gy per fraction (arm A, conventional fractionation) or 62 Gy in 20 fractions in 5 weeks (4 fractions per week) at 3.1 Gy per fraction (arm B, hypofractionation) to the prostate. The two arms were hypothesized to be isoeffective with regard to tumor control. However, with regard to late complications, the hypofractionation regime of this trial should be equivalent to 75 Gy given at 2.0 Gy per fraction that is lower than 80 Gy given in the conventional fractionation arm. From the data available in the literature and using the Lyman-Burman-Kutcher (LBK) model the 3-year rates of grade 2 or higher late rectal damage were estimated to be approximately 29% and 12% after 80 or 75 Gy, respectively, delivered at 2.0 Gy per fraction. On the basis of an 80% power to detect a significant difference (p<0.05, two sided), 84 patients were required in each arm (168 patients in total).

Late toxicity and outcome will be analyzed after median follow-up has reached 3 years.

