**03 Trial objectives**

**3.1** *Primary objective*

Reduction of late toxicity while maintaining the same Freedom from biochemical failure (FFBF) by hypofractionation with respect to conventional fractionation radiotherapy .

**3.2** *Secondary objective.*

Overall survival, Cause-specific survival, local, regional and distant control.

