**06 Therapeutic regimens**

**6.1** *Hormonal Therapy*

**6.1.1** *LHRH Analogues:* an LHRH analog depot (preferably Goserelin 10.8 g) will be administered with a subcutaneous injection at days 7, 97 and 187.

**6.1.2** *Antiandrogens:* the non-steroid antiandrogen *bicalutamide* will be orally administered at a daily dose of 50 mg for 270 days beginning at day 0 (7 days before the first LHRH analogue administration).

**6.2** *Radiotherapy*

The radiotherapy treatment will start at day 67 from the beginning of oral bicalutamide (60 days after the first LHRH analogue).

**6.2.1** *Patient data acquisition:* the treatment planning will be based on TC data acquisition. The volumes of interest (VOI) will be delineated on TC slices, taken at a minimum interval of 5 mm.

**6.2.2** *Target volumes:* The clinical target volume **(CTV)** is the prostate plus the entire SV. Planning target volume **(PTV)** = CTV + margin (according to institutional policy):

|  |  | |  | | | |
| --- | --- | --- | --- | --- | --- | --- |
|  |  |  |  |
|  |  |  |  |  |  |  |
|  |  |  |  |  |  |  |
|  |  |  |  |  |  |  |
|  |  |  |  |  |
|  |  |  |  |  |  |  |
|  |  |  |  |  |

**6.2.3** *Delineation of VOI:* The following volumes will be outlined on the planning CT: CTV, PTV, rectum from the inferior margin of the anus to the rectal- sigmoid junction, bladder, femoral heads. For rectum and bladder, where is possible the *wall* will be delineated; if the internal border of the bladder is not evident, a contour of 4 mm will be delineated.

**6.2.4** *Dose prescription:* Dose is specified to the ICRU reference point, positioned at the isocenter and/or close to the PTV center. Minimal and maximal dose to the PTV is 95% to 107% if achievable with respect to normal tissue dose-volume constraints, which have priority over the 95% dose-coverage of the PTV. Minimal dose to the CTV is 95%. Dose distribution and Dose-Volume Histograms must be accurately recorded.

**6.2.5** *Treatment technique:* Patients will receive either 3D-CRT **6.2.6** *Patient treatment position:* Supine. Personalized body-fix device with ankles support

**6.2.7** *Treatment verification:* the verification of the treatment position with respect to the DRR will be done at least twice a week by the individual institutional method (portal imaging, optic, X-ray or ultrasound device).

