**07 Randomization**

All patients will receive a total AD for 9-months and will be randomly assigned to one of the following radiotherapy schedules:

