**08 Evaluation**

**8.1** *Endpoints*

**8.1.1** *Freedom From Biochemical Failure (FFBF):* time interval from the randomization day to the biochemical relapse defined according to the most recent ASTRO Phoenix definition of nadir PSA +2 ng/ml (21).

**8.1.2** *Acute Toxicity:* Acute toxicity will be assessed using the RTOG/EORTC system (22) extended with a few symptoms not mentioned in the RTOG/EORTC acute radiation toxicity scale. Even a single-occasion symptom above baseline will be scored as toxicity. The AUA symptom index for BPH will be used to evaluate obstructive urinary symptoms (23). The AUA form has to be filled in by the patient (see Appendix)

**8.1.3** *Late Toxicity:* Late side effects will be assessed using a modified ("clinical") SOMA/LENT (24), in which side effects that can only be assessed by laboratory/technical investigations are eliminated. The AUA symptom index for BPH will be used to evaluate obstructive urinary symptoms. The AUA forms will be completed by the patient.

**8.1.4** *Disease-Free Survival (DFS):* time interval from the randomization day to the first clinical sign of disease progression.

**8.1.5** *Disease-Specific Survival (DSS):* time interval from the randomization day to the death for disease, with the exclusion of deaths for other diseases.

**8.1.6** *Overall Survival (OS):* time interval from the randomization day to death for any cause.

**8.2** *Timing*

**8.2.1.***Before treatment*

**a.** *Clinical Examinations*

- General examination

- WHO Performance Status (PS)

- Digital rectal examination with the evaluation of tumor diameter.

**b.** *Instrumental Examination*

- TRUS or MR for the evaluation of tumor local extension

- Pelvic CT or MR

- Multiple sextant prostate biopsy for the definition of Gleason Score

- Anorectal endoscopy for the baseline evaluation of the rectal mucosa (see

in the appendix).

- Bone scan

**c.** *Laboratory examinations*

- Baseline PSA determination

- WBC, RBC, and Platelet count, with HG determination

- Serum Testosteron and Dihydrotestosteron determination

- Histology with GS evaluation

**8.2.2** *During the radiotherapy treatment*

Acute toxicity will be assessed:

- at baseline (prior to radiation)

- once a week during radiotherapy

- 1 and 2 months after the end of radiation (where the acute period by definition terminates).

**8.2.3** *During the follow-up period*

**a.** *Instrumental, Clinical and Laboratory Examinations:*

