*-* PSA determination every 3 months for 3 years and then every 6 months.

- Testosteron and Dihydrotestosteron determination every 6 months for 3 years.

- DRE every 6 months for 3 years and, then, every 12 months

- TRUS or MR every 6 months until complete tumor clearance.

- Ano-rectal endoscopy every 6 months for 2 years.

- Sextant biopsies 2 years after the end of radiotherapy.

- Evaluation of the late toxicity every 6 months for 3 years, and yearly thereafter.

**8.2.5** *Summary of the examination timing*

|  | Baseline  evaluation | During  RT | Every 3mo.  for 3 yrs, then every 6 mo. | Every 6mo.  for 3 yrs.,  then yearly | At 2 yrs. or for suspected  Progression |
| --- | --- | --- | --- | --- | --- |
| **Clinical** | X |  |  | X |  |
| General | X |  |  | X |  |
| PS | X |  |  | X |  |
| DRE | X | X (RT end) |  | X |  |
| Acute Tox |  | X (weekly) |  |  |  |
| Late Tox |  |  |  | X |  |
|  |  |  |  |  |  |
| **Instrumental** |  |  |  |  |  |
| TRUS/RM | X |  |  | X (till CR) | X |
| Sextant biopsy | X |  |  |  | X |
| Ano-rectal endo | X |  |  | X (for 2 yrs) | X |
| Pelvic CT/MR | X |  |  |  | X |
| Bone scan | X |  |  |  | X |
|  |  |  |  |  |  |
| **Laboratory** |  |  |  |  |  |
| PSA | X | X (baseline)  X (RT end) | X |  | X |
| Histology (GS) | X |  |  |  | X |
| Blood count | X | X (weekly) |  |  |  |
| Testosteron/  dihidrotestosteron | X |  |  | X (for 3 Yrs) |  |

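### One analysis date at a 3-year median serves both late toxicity and tumour outcome; it suits toxicity but is too early for FFBF and survival to show more than a wide estimate

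*Protocol*

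**What the plan says.** Section 10 gives one date for everything: "Late toxicity and outcome will be analyzed after median follow-up has reached 3 years". It names no later analysis, event target or minimum follow-up, and does not say from which day follow-up is counted.

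Section 3.1 couples two aims in the primary objective: less late toxicity, and FFBF no different from conventional fractionation. Section 3.2 adds "Overall survival, Cause-specific survival, local, regional and distant control". Section 10 sizes the trial on toxicity alone, from 3-year rates of grade 2 or higher rectal damage of 29% and 12%, giving 84 patients per arm.

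The tumour clocks start at randomisation. FFBF in 8.1.1 is the "time interval from the randomization day to the biochemical relapse defined according to the most recent ASTRO Phoenix definition of nadir PSA +2 ng/ml", and overall survival in 8.1.6 is the "time interval from the randomization day to death for any cause". Hormone treatment is common to both arms. Section 7 states "All patients will receive a total AD for 9-months", and under 6.1.2 bicalutamide is "orally administered at a daily dose of 50 mg for 270 days beginning at day 0".

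Follow-up does not stop at the analysis date. Section 8.2.3 schedules "PSA determination every 3 months for 3 years and then every 6 months", and DRE and late-toxicity assessment continue yearly after year 3. No analysis is tied to those later data.

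**The concern.** A date chosen to fit a 3-year toxicity rate is also the date on which tumour control is judged. Relapse and death accumulate over a longer period than rectal damage, and some of the first 3 years is spent on androgen deprivation. If few failures have been seen, the confidence interval for the FFBF comparison is wide, and a non-significant difference could be read as meeting the second half of the primary objective. The population is high-risk, so the cost of wrongly concluding that control is preserved is substantial. The protocol's own background (section 01) cites tumour control after hypofractionation at 5 years, where one randomised trial found 59.95% against 52.95% biochemical failure.

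**Working it through.** **The plan's own figure.** With unpooled variances, n per arm = (1.960 + 0.842)² × (0.29 × 0.71 + 0.12 × 0.88) / 0.17² = 84.6, in line with the stated 84. The size and the 3-year date are coherent for toxicity. Neither was derived for FFBF.

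**Inputs from the protocol.** 168 patients, 1:1; 270 days (0.75 year) of androgen deprivation in both arms; a median follow-up of 3 years.

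**Assumptions (not in the protocol).** Follow-up counted from randomisation; uniform accrual over 3.5 years, so follow-up at a median of m years runs from m − 1.75 to m + 1.75; no failure during the lag L = 0.75 year; constant hazard afterwards; no dropout; 5-year failure f of 15% to 53%. The upper value is close to the lower of the two rates quoted in section 01, which come from a different (T1-T2) population.

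**Formulas.**
- Hazard after the lag: λ = −ln(1 − f) / (5 − L).
- Expected events: D = 168 × {1 − [exp(−λ(a − L)) − exp(−λ(b − L))] / (λ(b − a))}, with a = m − 1.75 and b = m + 1.75.
- 95% CI factor on the hazard ratio: exp(1.96 × 2/√D).

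**Worked case, f = 25%.** λ = 0.2877/4.25 = 0.0677.
- m = 3 (a = 1.25, b = 4.75): D = 168 × [1 − (0.9667 − 0.7628)/0.2369] = 23.4; factor exp(3.92/4.84) = 2.25.
- m = 5 (a = 3.25, b = 6.75): D = 168 × [1 − (0.8443 − 0.6662)/0.2369] = 41.7; factor 1.83.

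| Assumed 5-year failure | Events, 3-year median | CI factor | Events, 5-year median | CI factor |
|---|---|---|---|---|
| 15% | 13.7 | 2.9 | 25.1 | 2.2 |
| 25% | 23.4 | 2.25 | 41.7 | 1.83 |
| 35% | 33.6 | 2.0 | 58.2 | 1.7 |
| 53% | 53.5 | 1.7 | 87.8 | 1.5 |

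The later date gives 1.6 to 1.8 times the events (87.8/53.5 = 1.6; 25.1/13.7 = 1.8). If the event-free period is assumed to last 1.25 years, the ratio reaches 2.1 (25.1/12.1 at f = 15%). Changing accrual between 0 and 4 years moves any of these counts by no more than about 2 or 3.

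**What the width means.** If the observed hazard ratio were exactly 1, the 3-year interval would run from 1/2.25 = 0.44 to 2.25 at f = 25%, and from 1/1.71 = 0.58 to 1.71 at f = 53%. As a difference in 3-year FFBF with 84 per arm, all followed to 3 years, the half-width is 1.96 × √(2p(1 − p)/84): ±9, ±12 or ±14 percentage points for p = 90%, 80% or 70%. A 3-year median is less favourable, since half the patients have shorter follow-up.

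**Share due to androgen deprivation.** Holding 5-year failure at 25%, removing the lag raises the 3-year count only from 23.4 to 26.4.

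**Deaths.** With assumed 5-year overall survival of 95% to 85% and no lag, the same formula gives 5.1 to 15.5 deaths in both arms together at a 3-year median.

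**The case against.** Several stronger readings are tempting, and the objections to them stand.

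- *That androgen deprivation pushes the FFBF curves together, so the arms are bound to look alike.* An event-free interval shared by both arms lowers the event count but does not pull the hazard ratio towards 1. Restarting the clock at day 270 would be no remedy: if nobody fails earlier, it subtracts a constant from every time and leaves the log-rank and Cox results essentially unchanged. That no failure occurs under suppression is itself a modelling assumption; the protocol does not say it.
- *That hardly any FFBF events can have occurred.* This depends on the assumed rate. At 53% failure there would be about 54 events at 3 years, which is limited but not negligible. Sparse data are a safer expectation for deaths.
- *That the protocol rules out any later analysis.* The wording sets an earliest date, follow-up continues with no stated end, and an analysis plan that is not shown might add an update. The point is only that section 10 fixes this one date for both purposes.
- *That the 5-year figure in the background is a criterion for this trial.* It is a cited result, not an adopted benchmark.

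It is also fair that survival is secondary with no power claimed, and that timing is not the largest gap. The FFBF aim has no margin, event target or sample size, and waiting until 5 years does not repair that. What the objections leave untouched is that half of the primary objective is tied to a date chosen for the other half.

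**Conclusion.** The concern holds as one of imprecision. At a 3-year median the FFBF comparison would rest on about 14 to 54 events, with 95% limits a factor of 2.9 to 1.7 either side of the hazard ratio; about 5 to 16 deaths would be available for survival. A 5-year median would give about 25 to 88 FFBF events and a factor of 2.2 to 1.5. Over the whole assumed range, a non-significant FFBF result at 3 years cannot tell similar control from meaningfully worse control.

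The counts rest on assumed failure and death rates, constant hazard after a 9-month lag, 3.5-year accrual and follow-up counted from randomisation; none of these is in the protocol. The gain from the later date is less sensitive to them than the counts are. A reader should not infer that the design biases the comparison towards equality, or that a 5-year reading would prove it. This is a cheap improvement to the plan, not a flaw that invalidates the toxicity result.

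**What to change.** Split the closing sentence of section 10.

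1. Keep the 3-year median for late toxicity, and state the day from which follow-up is counted.
2. State that FFBF and survival at that date are descriptive, reported with confidence intervals, and support no claim that tumour control is preserved.
3. Add a main FFBF analysis, together with overall and cause-specific survival and local, regional and distant control, at a median follow-up of at least 5 years.
4. State that even this later result is an estimate with its confidence interval and not a demonstration of sameness, because no margin is set.

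The cost is wording and one further analysis. No extra patients or visits are needed, because PSA and clinical follow-up are already scheduled after year 3. The downside is that the tumour-control result arrives about 2 years after the toxicity result.

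### The 84 per arm assumes every patient's 3-year toxicity status is known, but the analysis may start at a median follow-up of 3 years, so the stated 80% power is not delivered for the 3-year rate

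*Protocol*

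**What the plan says.** Protocol section 10 contains both the sizing and the timing.

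- **Effect assumed:** 3-year rates of grade 2 or higher late rectal damage, "approximately 29% and 12% after 80 or 75 Gy, respectively, delivered at 2.0 Gy per fraction". Section 10 treats the hypofractionated arm as equivalent to the lower of these two doses for late complications.
- **Error rates:** "On the basis of an 80% power to detect a significant difference", at a two-sided 5% level.
- **Result:** "84 patients were required in each arm (168 patients in total"). The number required is also the number to be randomised, with nothing added for death or loss.
- **Timing:** "Late toxicity and outcome will be analyzed after median follow-up has reached 3 years".

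Section 8.2.3 sets the visits: "Evaluation of the late toxicity every 6 months for 3 years, and yearly thereafter". The 3-year visit therefore closes the window to which the 29% and 12% refer. The protocol gives no accrual period, minimum follow-up or expected loss rate.

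**The concern.** A 3-year proportion computed on 84 patients per arm needs 84 known 3-year outcomes per arm. When the median follow-up has just reached 3 years, about half the patients have not yet had 3 years. The sizing and the trigger therefore describe different data sets, and the sizing has no margin to absorb the difference.

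What is at stake is the power on the endpoint for which the trial was sized. If the late-rectal-toxicity comparison is not significant, part of the explanation could be incomplete follow-up rather than the absence of the assumed 17-point difference. The stated 80% would not tell a reader that.

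**Working it through.** **Inputs from protocol section 10:** p_A = 0.29, p_B = 0.12, two-sided alpha 0.05, power 80%, 84 per arm.

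**1. Reproduce the 84.** Two proportions, unpooled variance:

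n = (1.960 + 0.842)² × (0.29×0.71 + 0.12×0.88) / 0.17² = 7.85 × (0.2059 + 0.1056) / 0.0289 ≈ 84.6 per arm.

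The arcsine formula gives 84.95, the pooled-variance formula 88, and the version with continuity correction 99. So 84 is a fixed-time, complete-data figure with no inflation.

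**2. Power at 84 per arm with all outcomes known.**

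- Unpooled: SE = √(0.3115/84) = 0.0609; 0.17/0.0609 − 1.960 = 0.83; power 79.7%.
- Pooled: mean rate 0.205; null SE = √(2×0.205×0.795/84) = 0.0623; (0.17 − 1.960×0.0623)/0.0609 = 0.79; power 78.4%.

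**3. What the trigger yields.** The accrual period is not given, so it is assumed uniform over A years. If the analysis takes place when the median is exactly 3 years, follow-up ranges from 3 − A/2 to 3 + A/2 years. For A = 4 that is 1 to 5 years.

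**4. Power at that date, by simulation** (84 per arm, 2,000 replicates per cell, simulation standard error about 1 point, no losses). Two event-timing patterns, both giving 29% and 12% at 3 years:

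- *Continuing:* constant hazards of −ln(0.71)/3 = 0.114 and −ln(0.88)/3 = 0.043 per year.
- *Stopping:* 40% of the 3-year events by year 1, 80% by year 2, all by year 3, none later.

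| Accrual A | KM at 3 y, continuing | KM at 3 y, stopping | Log-rank, continuing | Log-rank, stopping |
|---|---|---|---|---|
| 0 (all at 3 y) | 79.6% | 81.3% | 78.7% | 80.7% |
| 2 years | 75.5% | 77.4% | 79.7% | 77.1% |
| 3 years | 70.2% | 76.7% | 78.2% | 76.1% |
| 4 years | 68.9% | 72.4% | 78.1% | 72.4% |

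The first row recovers the complete-data power, which checks the method. Other assumed timings widen the ranges a little. Over Weibull hazard shapes 0.7 to 1.5, the Kaplan-Meier figure falls to about 67% at the low end. Other timings of events that all fall within 3 years take the log-rank figure down to about 69%. With 1-year accrual the Kaplan-Meier comparison has 77–78%.

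**5. With losses.** At an assumed 4% per year death or loss and 2–4 years of accrual, the Kaplan-Meier comparison has about 65–73% and the log-rank test about 75–78% if toxicity continues.

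**6. If every patient has at least 3 years of potential follow-up.** The Kaplan-Meier comparison has about 80% without losses and about 78% with 4% per year loss.

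**The case against.** The strongest reply is that the protocol does not name the test. It uses 3-year rates for sizing and then says only that late toxicity will be analysed; the method may be in an analysis plan that is not shown. Censored patients still contribute to a time-to-event analysis, and a log-rank test over all follow-up keeps 78–80% if toxicity continues beyond 3 years, so the trigger would then cost almost nothing. This stands, and it is why the conclusion is confined to the 3-year rate. It is not a general rescue, because the same test falls to about 69–77% if events stop by 3 years.

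Two further replies stand. The trigger is an earliest date, so half the patients being short of 3 years is the upper limit. And the shortfall depends on accrual, which is not stated: with 1-year accrual it is only about 2 points.

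Two stronger readings are tempting but not supported:

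- A reader might infer that power is roughly halved, because only about 42 per arm have a full 3 years; 42 per arm gives 49–51%. That requires discarding every patient censored before 3 years, which nothing in the protocol proposes. It is a bound, not a planned analysis.
- A reader might infer that the early date also tilts the comparison of freedom from biochemical failure towards a finding of no difference, given 270 days of androgen deprivation (section 6.1.2). The protocol gives no failure rates from which to compute this, and the effect would depend on how equivalence is judged. Moving the trigger would barely help: the last patient at 3 years would still be only about 3 − 270/365 ≈ 2.3 years past the end of that treatment. It is no part of this point.

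**Conclusion.** The mismatch is real and lies within section 10 itself. The 84 per arm delivers about 80% only if all 3-year outcomes are known, and the trigger permits analysis before they are.

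For the 3-year rate, measured against the complete-data 78–80%, the loss ranges from about 2 points with 1-year accrual to somewhat more than 10 points with 4-year accrual at the less favourable event timings. An assumed 4% per year loss lowers power further, but that part reflects the missing loss allowance rather than the trigger. For a log-rank test over all follow-up, the loss runs from nearly nothing to about 10 points, depending on whether toxicity continues after 3 years.

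These figures rest on assumed uniform accrual, assumed event timing and analysis at the moment the median reaches 3 years. The direction for the 3-year rate does not depend on the particular accrual length; the size does. This is a moderate correction, not a fault that invalidates the design.

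**What to change.** Amend section 10 in one of two ways. Neither needs extra patients.

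1. **Match the trigger to the sizing.** Make the 3-year late-toxicity comparison when the last randomised patient has, or would have, completed the 3-year late-toxicity visit. Power is then about 80% without losses and about 78% with 4% per year loss. The cost is time: under uniform accrual the median reaches 3 years at 3 + A/2 years from the first patient and the last patient reaches 3 years at 3 + A, a delay of A/2, or 1–2 years for accrual of 2–4 years.
2. **Match the analysis to the trigger.** Keep the median-based date, name a time-to-event comparison over all follow-up as the primary toxicity test, and restate its power at that date with explicit accrual, loss and event-timing assumptions. The cost is a recalculation and a power figure that may come out below 80%.
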